Message framing is the presentation of information in a way that affects the perception, attitude, or behavior of the person receiving it. It is how a message is worded, structured, or framed to impact the target audience’s perception and persuade them to take action [21,22]. There are 2 primary forms of message framing: gain-framing and loss-framing. Gain-framing highlights the advantages or positive results of a decision or action, while loss-framing focuses on the potential negative consequences or losses that could result. The type of framing used depends on the context and objectives of the message, as it can be used to either encourage or discourage specific actions [23,24]. Scholars have been reporting that gain-framed information is more persuasive for disease prevention behaviors as it encourages risk aversion and thus engages in safe disease prevention behaviors. Conversely, loss-framed information is suggested for disease detection behaviors, as it makes people willing to take risks and engage in relatively risky disease detection behaviors [25,26].

The literature on health message framing is extensive and has shown promising effects on health outcomes, including maternal and child health [27,28]. A study by Divdar et al [28] showed significant improvements in oral health knowledge, attitude, intention, efficacy, and practice among the intervention group as compared to the control group, although no significant difference was observed between gain and loss-framed messages. Both gain and loss-framed messages significantly improved breastfeeding self-efficacy in a study conducted in Iran [29]. Another 3-arm intervention has shown significant improvements in complementary feeding knowledge, attitude, self-efficacy, and practice among interventions, with the loss-framed group showing higher improvement than the gain-framed group [30]. However, Frew et al [31] found is no improvement in maternal influenza immunization in their intervention evaluating message framing. These findings indicate inconsistent results regarding which framing method improves maternal and child health care practices [29-31]. Moreover, the evidence on the impact of message framing on maternal and newborn care practice is still unclear in LMICs and needs further assessment [32]. Therefore, to foster our understanding of framing effects and determine which way of information framing has a strong persuasive effect on maternal and newborn health, we need further confirmation.

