### Sample Size Determination

#### Sample Size for the ANC Visit

The method suggested by Hooper et al [34] for cluster randomized trials with repeated cross-sections was used for the calculations. This method requires calculating 2 design effects, which are then used to inflate the sample size for individual randomization to account for the within-period intracluster correlation coefficient (ICC) and the between-period ICC. A sequence of steps has been followed to get the final sample size for the current 3-arm cluster randomized trials with repeated cross-sections. For ANC, we first calculated the individual randomization trial using the following assumptions: P1—the proportion of women attending ANC for more than 4 visits among the control group 23.27% [35], power=80%, 2-sided α=0.025, effect size=15%, and Zα/2 adjusted for multiple comparisons using a Bonferroni correction of 2.24. Individual randomization sample size (n) is calculated as follows:

Next, the design effect (*d*_c_) due to cluster randomization was calculated as *d_c_* = 1 + (*m* – 1)*ρ*. Here, the following parameters were considered: the within-period ICC(*p*) was assumed to be 0.003 [36], and the cluster size (m) was assumed to be 28. The calculation yielded a design effect due to cluster randomization *dc* = 1 + (*m* – 1)*ρ* = 1.08. Additionally, the design effect due to repeated assessment was calculated as *d*_r_=(1–*r*^2^), where *r* is the correlation between samples from the same cluster at different times and determined as 
[figure not shown]
. Based on this, *d*_r_ was calculated using assumptions: within-period ICC=0.003, autocorrelation coefficient (π) of 0.8 (to allow for a 20% decay of the correlation from within to between different periods) [37], and *m*=28 and 
[figure not shown]
=0.062. Thus, the design effect due to repeated assessment was *d*_r_=(1–*r*^2^)=0.996.

To arrive at the final sample size per arm, the sample size for individual randomization is multiplied by both design effects, resulting in (n×*d*_c_×*d*_r_)=188. Considering a 4% loss to follow-up, the final sample size for each arm is 196 and this gives a total sample size of 588 when ANC was used as the primary outcome of the intervention.

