#### Sample Size for Newborn Practice

For newborn care practice, the same procedure described earlier was used. First, the individual randomization sample size was calculated to be 118 based on the following assumptions: P1—the proportion of exclusive breast feeding among the control group of 74.8% [38], power=80%, 2-sided α of 0.025, effect size=15%, and *Z*α/2 adjusted for multiple comparisons using a Bonferroni correction=2.24. Then, the design effect (*d*_c_) due to cluster randomization was calculated as *d_c_* = 1 + (*m* – 1)*ρ* = 1.35 by considering the following parameters: within-period *p* of 0.013 [39] and cluster size assumed to be 28. The design effect due to repeated assessment was calculated as *d*_r_=(1–*r*^2^)=0.953, where the correlation between samples from the same cluster at different times *r*=0.251 by using assumptions: within-period ICC=0.013 [39], autocorrelation coefficient (π) of 0.8 (to allow for a 20% decay of the correlation from within to between different periods) [37], and *m*=28. By inflating the sample size under individual randomization with the 2 design effects as (n×*d*_c_×*d*_r_)=152. Considering a 4% loss to follow-up, the total sample size was 475.

Therefore, the sample calculated for ANC was larger (588) and was the final sample size of the trial to arrive at 21 clusters (7 per arm) and an average of 28 eligible pregnant mothers.

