**Primary outcomes**
Maternal health service usageNewborn care practice

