### Data Analysis Plan

Double-data entry was accomplished using Epi-data (version 4.6, released in 2020; the EpiData Association) and exported to the SPSS (version 25; IBM Corp) for analysis. The report of this study will be made according to the CONSORT-EHEALTH (Consolidated Standards of Reporting Trials of Electronic and Mobile HEalth Applications and onLine TeleHealth) standards for reporting randomized controlled trials. Exploratory subgroup analysis was done to identify whether the effects of intervention vary with sociodemographic characteristics, socioeconomic characteristics, obstetric history, and psychological factors. To assess the characteristics of the study population through the lenses of different variables, selected data were tabulated by study arms; this helped us to identify variations and similarities among study arms. The summary statistics used for categorical variables were frequencies and percentages. For continuous variables, the mean and standard deviation will be presented.

To observe the effectiveness of mobile phone messaging-based message framing interventions for improving maternal and newborn health service usage, we will use an intention-to-treat approach where all randomized participants will be included in the statistical analysis, regardless of whether they received the intervention or not. A generalized linear mixed model will be used to adjust for both the clustering effect and the participant-level intracluster correction. The outcome variables are assumed to have a multivariable normal distribution. The odds ratio will be used to measure the effectiveness of the intervention on the outcome variable with a 95% CI.

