## Discussion

### Major Findings

This study aims to evaluate the effectiveness of mobile phone messaging–based message framing interventions for improving maternal and newborn health practices. We hypothesize that increased usage of maternal and newborn care services in the intervention group exposed to mobile-based message framing (gain-framed and loss-framed messages) was comparable to that in the control arm. This trial is designed with the assumption of achieving improvements in key indicators such as 8-time antenatal care visits, increased health facility deliveries, increased postpartum attendance, and improved newborn care practice. Previous studies indicate that mobile phone interventions during pregnancy have a positive effect on maternal health outcomes. For instance, text messaging interventions have shown potential for informing, motivating, and reminding pregnant and postpartum women about timely health care usage, which leads to positive maternal and child health outcomes [40-43].

Our intervention focuses on message framing for the early enrollment of pregnant women on the continuum of care. Pregnant mothers with a GA of 16-20 weeks are preferred based on the World Health Organization’s recommendations for early antenatal care initiation. Previous studies evaluating the effectiveness of SMS-based interventions to improve maternal and neonatal health selected pregnant women who had already started antenatal care visits and used health facilities [12,44-46].

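### Both primary outcomes are sized at two-sided 0.025 (z = 2.24), but effectiveness is to be measured with 95% confidence intervals, so the Bonferroni correction does not reach the analysis

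*Protocol article*

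**What the plan says.** The section Sample Size for the ANC Visit takes "2-sided α=0.025, effect size=15" (in percentage points), 80% power, and a z value "adjusted for multiple comparisons using a Bonferroni correction of 2.24". The section Sample Size for Newborn Practice repeats "2-sided α of 0.025, effect size=15" and the same 2.24 for the second outcome. The larger of the two results, 588 women, became the trial size.

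Textbox 1 lists two primary outcomes, maternal health service usage and newborn care practice. There are three arms: gain-framed, loss-framed and usual care. The article does not say whether success needs one primary outcome or both.

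The Data Analysis Plan specifies intention to treat and a generalized linear mixed model, and then: "The odds ratio will be used to measure the effectiveness of the intervention on the outcome variable with a 95% CI". It mentions neither 0.025 nor 2.24, and no adjustment for multiple comparisons.

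**The concern.** Two parts of the same document use different error levels for the same comparisons. A critical value of 2.24 goes with a 97.5% interval; a 95% interval goes with 1.96. A reader who follows the Data Analysis Plan literally would call a message arm effective on weaker evidence than the sample size assumed.

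The split by two also covers only one of two sources of multiplicity. The article does not say which two comparisons it means; the natural reading is each message arm against control. The full 0.025 is then spent again on the second primary outcome. If the split was meant for the two outcomes instead, the two arms are uncovered. Either way there are four control comparisons.

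The article expects the results to inform a decision by policy makers to scale up, so a false claim for one framing would matter.

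**Working it through.** **1. Reproduce the sizing, to confirm that 0.025 is the level it rests on.** Inputs from the two sample size sections: ANC 23.27% versus 38.27%, ICC 0.003; newborn care 74.8% versus 89.8%, ICC 0.013; for both, m = 28, autocorrelation 0.8, 80% power, 4% loss. The equation images are missing from the text at hand, so these forms are inferred from the match with the stated results:

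- n = (z_α/2 + z_β)² [p1(1 − p1) + p2(1 − p2)] / d²
- d_c = 1 + (m − 1)ρ; r = mρπ / [1 + (m − 1)ρ]; d_r = 1 − r²

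ANC: (2.2414 + 0.8416)² × (0.1786 + 0.2362) / 0.15² = 175.2. With d_c = 1.081, r = 0.062 and d_r = 0.996, the product is 188.7 (stated 188). Then 188 / 0.96 gives 196 per arm and 3 × 196 = 588. This matches.

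Newborn care: n = 118.3 (stated 118), d_c = 1.351, d_r = 0.953, product 152.4 (stated 152), total 3 × 152 / 0.96 = 475. This matches.

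At two-sided 0.05 the ANC calculation would give 144.7, or 155.8 after the design effects. The stricter level therefore accounts for about 188.7 − 155.8 = 33 women per arm.

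**2. False positives under each interval level.** Method: 1,000,000 simulated null trials with three equal arms and normal arm means; contrasts gain − control and loss − control share the control arm; the second outcome has correlation ρ with the first. The correlation between outcomes is not in the article, so a range is shown. An interval excluding 1 is taken as a positive result.

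| Two control contrasts | 95% CI (1.96) | 97.5% CI (2.24) |
|---|---|---|
| One outcome | 9.1% | 4.7% |
| Win on either outcome, ρ = 0 | 17.3% | 9.1% |
| ρ = 0.3 | 16.9% | 8.9% |
| ρ = 0.5 | 16.1% | 8.5% |
| ρ = 0.7 | 14.9% | 7.9% |
| ρ = 0.9 | 12.6% | 6.6% |

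Hand check at ρ = 0: 1 − (1 − 0.0907)² = 0.173 and 1 − (1 − 0.0466)² = 0.091.

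**3. If an arm had to win on both outcomes.** With no effect on either outcome, the chance of a false claim at 95% is only about 0.5% (ρ = 0) to 1.8% (ρ = 0.5). But if both message arms truly improve one outcome, and trials nearly always detect it, the claim turns on the other outcome alone and the chance goes back up towards 9.1%. Requiring both removes the multiplicity over outcomes, not that over arms.

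**4. Price of matching the sizing level.** Interval width on the log odds scale rises by 2.2414 / 1.9600 = 1.14, about 14%.

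**The case against.** The strongest reply is that a 95% interval is a reporting format, not a decision rule. The Data Analysis Plan does not say that an interval excluding 1 counts as a win, and 95% intervals can stand beside tests at 0.025. A fuller analysis plan may exist and settle the test level and the handling of two primary outcomes. This stands to the extent that every error rate above is conditional on reading the interval as the test. It does not remove the mismatch: the only sentence on how effectiveness will be measured uses a different level from the one that set the sample size.

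It is also fair that nothing in the article promises a 5% error rate across both outcomes together, and that each outcome was sized separately. The 13–17% is therefore a consequence of one possible success rule, not of the stated plan.

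A reader might infer more, in two ways that the article does not support.

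- **An overall error rate of 16–23%.** That range needs a win on either outcome and an outcome correlation of 0 to 0.5. Its upper part (21–23%) also needs gain versus loss as a third confirmatory contrast. The Background does want to "determine which way of information framing has a strong persuasive effect on maternal and newborn health", but that is motivation. The objective stated at the end of the Background concerns the effect of gain- or loss-framed messages on usage and practice, and neither sizing section nor the Data Analysis Plan names a gain-versus-loss test.
- **An equivalence hypothesis.** Major Findings says that usage in the intervention group "exposed to mobile-based message framing (gain-framed and loss-framed messages) was comparable to that in the control arm". The next sentence assumes improvements in the key indicators, and the sizing assumes a 15-point difference, so this is a wording slip. It should be corrected but adds nothing to the error rate.

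**Conclusion.** The point holds as an internal inconsistency: sizing at two-sided 0.025, analysis with 95% intervals. On the most direct reading, one outcome with two control comparisons and the interval read as the test, the false positive chance is about 9.1% instead of about 4.7%. This needs no assumption about the correlation between outcomes.

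The larger figures, about 13–17% at 95% and about 7–9% at 97.5%, apply only if a win on either primary outcome counts. They rest on an assumed correlation between 0.9 and 0. They show why 97.5% intervals alone do not settle the matter while the rule for combining the two outcomes is unstated.

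**What to change.** 1. In the Data Analysis Plan, report 97.5% intervals, and test at 0.025, for gain versus control and loss versus control, to match z = 2.24. Cost: intervals about 14% wider on the log odds scale. No power is lost against the sizing, which already assumed this level.

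2. State, before arm comparisons are seen, how the two primary outcomes combine. The article describes the analysis as still pending; if comparisons have been seen by the time of the change, disclose this. The options are:
   - **Both required** for an arm, each at 0.025.
   - **A fixed order** within each arm at 0.025, which bounds the overall error at 2 × 0.025 = 5%. The second outcome cannot be claimed for an arm that fails the first. The power of the first step is not established if maternal health service usage leads: Operational Definitions makes it a composite of at least 8 ANC visits, facility birth and a postnatal contact within 7 days, while the sizing used "the proportion of women attending ANC for more than 4 visits among the control group 23.27% [35], power=80"%. The reverse order has a similar gap, since newborn care was sized on exclusive breastfeeding alone but is defined by several practices together.
   - **An alpha split**, for example 0.05 / 4 = 0.0125 per test. On the plan's own formula this needs 205.6 × 1.081 × 0.996 = about 221 per arm, 231 after 4% loss and 693 in total; at 188 analysed per arm the ANC power would be about 71–72%.

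3. Label gain versus loss as secondary or exploratory.

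4. In Major Findings, restate the hypothesis as superiority of each message arm over control.

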### Ethical Considerations

Ethical approval was received from the Jimma University Institutional Review Board (ref no JUIH/IRB/358/23). Participating in this trial was completely voluntary, and women can opt out of receiving the messages by sending “stop” to the domain. Informed consent was obtained for taking part in the intervention, baseline, and end-line assessments. The interviewer read the contents of the informed consent form and outlined the purpose of the study, the institutions and researchers involved, the expectations of women, and the risks and benefits associated with the trial using the local language. Women also get an explanation about their rights as participants and have their questions answered before enrollment.

Women’s phone numbers were kept encrypted, and no one could access them without a server technician and researcher. Codes were assigned to each enrolled woman to ensure confidentiality; mobile numbers were entered into the dashboard anonymously. Data were shared with the research team after removing participants’ names. No compensation was provided to participants for taking part in this trial.

### Monitoring

Monthly monitoring of intervention implementation was conducted by collecting data through face-to-face interviews using a predefined questionnaire. Participants were asked the number of maternal and newborn information they have received through SMS, the number of messages read, the service they have used following the received message, and any pregnancy outcomes. They were also asked about any barriers that they have faced to receive the messages and the usage of services after receiving messages. Moreover, the functionality and stability of the messaging system were monitored continuously for the duration of the project. Data about the SMSs being sent and delivered were also automatically recorded by the messaging system and checked weekly.

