**Methods:**

A 3-arm cluster-randomized trial design was used to evaluate the effects of mobile phone–based intervention on maternal and newborn health service usage. The trial arms were (1) gain-framed messages (2) loss-framed messages, and (3) usual care. A total of 21 health posts were randomized, and 588 pregnant women who had a gestational age of 16-20 weeks, irrespective of their antenatal care status, were randomly assigned to the trial arms. The intervention consisted of a series of messages dispatched from the date of enrolment until 6-8 months. The control group received existing care without messages. The primary outcomes were maternal health service usage and newborn care practice, while knowledge, attitude, self-efficacy, iron supplementation, and neonatal and maternal morbidity were secondary outcomes. The outcomes will be analyzed using a generalized linear mixed model and the findings will be reported according to the CONSORT-EHEALTH (Consolidated Standards of Reporting Trials of Electronic and Mobile HEalth Applications and onLine TeleHealth) statement for randomized controlled trials.

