#### Gain-Framed Message

Women in this arm received an automated gain-framed message. The gain-framed SMS text messages, which were tailored based on individual women’s gestational age (GA), expected delivery time, and postnatal period, were sent from the time of enrolment during ANC until the end of the postnatal period to the established list of participants’ phone numbers. Women in this group also received the existing maternal care provided at the health facility.

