#### Control Group

Participants in the control group received existing ANC and PNC services provided at health facilities. According to the recent ANC guidelines, pregnant mothers are expected to have 8 ANC and 3 PNC contacts. In addition to these cares, counseling services is recommended on the following topics during ANC visits: (1) lifestyle modification, (2) danger signs and symptoms, (3) birth preparedness and complication readiness, and (4) other issues such as family planning, cord care, bathing, breastfeeding, child immunization, and screening for cervical cancer [33].

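### Monthly face-to-face monitoring appears to have reached only the message arms; if so, each message-versus-control contrast tests SMS plus repeated interviews, not SMS alone

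*Protocol article*

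**What the plan says.** The protocol article's Gain-Framed Message and Loss-Framed Messages sections define each active arm as automated, tailored SMS on top of routine care. For the gain arm the text adds: "Women in this group also received the existing maternal care provided at the health facility". The Control Group section reads: "Participants in the control group received existing ANC and PNC services provided at health facilities". The abstract puts it more briefly: "The control group received existing care without messages". None of these descriptions mentions a monthly visit or interview.

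The Monitoring section then reports: "Monthly monitoring of intervention implementation was conducted by collecting data through face-to-face interviews using a predefined questionnaire". On content it says: "Participants were asked the number of maternal and newborn information they have received through SMS, the number of messages read, the service they have used". The same sentence goes on to pregnancy outcomes. It continues: "They were also asked about any barriers that they have faced to receive the messages and the usage of services after receiving messages". Separately, it describes an electronic record: "Data about the SMSs being sent and delivered were also automatically recorded by the messaging system and checked weekly".

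The section does not say which arms were interviewed. Strengths and Limitations does not discuss the interviews as a contact that could differ between arms.

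**The concern.** A monthly in-person interview about services used and obstacles to using them deals with the behaviour that the maternal primary outcome measures: antenatal visits, facility birth and early postnatal care. Repeated questions of this kind might prompt attendance. They might also shape what women report at the end-line, which is itself a face-to-face interview of unblinded participants.

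If only message-arm women had this contact, it coincides completely with being sent messages. Neither the intention-to-treat analysis nor the mixed model in the Data Analysis Plan can then separate the two. The Abstract (Conclusions) and the closing Conclusions section speak of what mobile messaging can achieve and of scaling it up. An automated SMS programme would not, on its description here, include a monthly visit. What is at stake is therefore attribution: which package the message-versus-control estimates describe.

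**Working it through.** The plan gives no figure on this point, so the check is mainly a comparison of sections, followed by a count of contacts and an illustration.

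**1. Who was interviewed?**
- The stated purpose is to monitor implementation of the intervention.
- Items on SMS received, messages read, services used after a message, and barriers to receiving messages or using services afterwards all presuppose messages. Only pregnancy outcomes is neutral between arms.
- Data Collection Procedures and Tools names a baseline and an end-line survey and no monthly survey. Ethical Considerations lists consent for the intervention, baseline and end-line, with no separate monthly assessment.
- Against this, the Monitoring section says only that participants were asked. Intervention Components and Results use participant wording that covers all three arms.

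Interviewing in the message arms only is therefore a strong inference, not a stated fact.

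**2. Does the topic overlap a primary outcome?** Operational Definitions sets maternal health service usage as at least 8 antenatal visits, a facility birth and postnatal contact within 7 days of delivery. The service-use and barrier items overlap this directly. They do not name newborn care practices, so the mechanism is weaker for the second primary outcome.

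**3. How many contacts could matter?** Inputs: gestational age 16-20 weeks at enrolment (Eligibility Criteria); recruitment in March 2023 and intervention from May to December 2023 (Results). Assumptions: birth at 40 weeks, and one interview per calendar month from May.
- Earliest: 20 weeks on 1 March, plus 20 weeks (140 days), gives 19 July. Adding 7 days gives 26 July. May, June and July make 3 contacts.
- Latest: 16 weeks on 31 March, plus 24 weeks (168 days), gives 15 September. Adding 7 days gives 22 September. May to September makes 5 contacts.
- May to December spans 8 calendar months, but later contacts cannot change the maternal outcome itself. They could still affect how it is reported in February 2024.

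If the first interview came a month after roll-out, each count falls by one.

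**4. What could a contact effect do?** The documents give no size, so this is an illustration over an assumed range. Inputs from Sample Size for the ANC Visit: control proportion 23.27%, two-sided α 0.025 (z = 2.24), 188 evaluable women per arm, design effects 1.08 and 0.996. Effective n per arm = 188 / (1.08 × 0.996) = 174.8. Suppose that SMS has no effect and contact raises the proportion by d, so p1 = 0.2327 and p2 = p1 + d. The chance of a significant result favouring messages is about Φ[(d − 2.24 × SE0) / SE1]. Here SE0 = √[2p̄(1 − p̄)/174.8], p̄ is the mean of p1 and p2, and SE1 = √[(p1(1 − p1) + p2(1 − p2))/174.8].
- d = 0: about 1.3%
- d = 3 points: about 5.6%
- d = 5 points: about 12%
- d = 10 points: about 43%

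These values refer to the planning endpoint (more than 4 antenatal visits), not the composite primary outcome. They show sensitivity only and are not evidence that a contact effect exists.

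**The case against.** The strongest reply is that the Monitoring section names no arm, that participants elsewhere means all three arms, and that a condensed article may leave the coverage of a process form to the full protocol. The first two points stand, which is why the conclusion is conditional. The third explains the omission, but the article still draws conclusions about messaging that depend on the answer.

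A reader might infer that the contrast is wrong whichever arms were interviewed. The documents do not support that. If controls were interviewed equally, general contact is largely balanced and only the message-linked items differ. Research interviews do not by themselves change usual care; controls also had baseline and end-line interviews.

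A reader might infer that the interviews were unnecessary because an electronic log existed. That fails too. The log covers sending and delivery, not reading. Eligibility and Recruitment allow a family member's phone, so delivery to a handset does not show that the woman saw the message. The adherence mediation analysis in Strengths and Limitations plausibly needs data on messages read.

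Two further points stand in part. The text describes a predefined questionnaire, with no counselling or reminders, so calling it active prompting goes beyond what is written. End-line interviewers were kept unaware of allocation, but this does not prevent unblinded women's own answers from being influenced.

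**Conclusion.** The point holds as a problem of attribution, conditional on who was interviewed. The wording strongly implies that only the message arms were. In that case each message-versus-control estimate compares SMS plus monthly face-to-face monitoring with usual care, and effects on service use or its self-report cannot be assigned to SMS alone. About 3 to 5 contacts could fall before the maternal outcome closes, given term birth and monthly interviews from May.

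It would be tempting to say that the bias favours the message arms or accounts for a set share of the 15-point planned effect. The documents give neither direction nor size, so no such figure is claimed. Nor does anything in the text propose taking primary outcomes from the monthly interviews. The gain-versus-loss contrast is unaffected if, as described, both message arms were monitored alike.

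**What to change.** Before the pending analysis is reported:

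- State in the Monitoring section which arms were interviewed each month.
- If only the message arms were, define and report each message-versus-control estimate as SMS plus monthly face-to-face monitoring versus usual care.
- Limit the Abstract conclusion and the scale-up statement in Conclusions to that package, and add the point to Strengths and Limitations.
- Name gain versus loss as the contrast that isolates message content.
- Keep the messages-read data for the adherence mediation analysis, and use the automatic log for sending and delivery.
- If controls were interviewed equally, say so. The contrast then needs no relabelling, only a note that the message-linked items applied to the message arms.

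The cost is a few sentences, with no new data and no change to sample size, outcomes or model. The downside is a narrower claim about SMS alone.
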